### Data-analysis

The trial statistician, who will be blinded to randomization, will carry out the data analysis process. Before analysis, they will assess the integrity of collected data, and repeated or missing data will be described accordingly. Demographics and repeatedly measured clinical characteristics of participants will be summarized as the baseline.

SPSS for Windows, version 25 (IBM Corp, Armonk, NY), and GraphPad Prism for Windows, version 8.0.0 (GraphPad Software, San Diego, California), are used for data analysis. Continuous data are shown as the mean and standard deviation. Categorical variables are represented as percentages. Continuous variables are compared using the Mann–Whitney *U* test. Categorical variables are compared between groups using Fisher’s exact test or the chi-square test. Fisher’s exact test or the chi-square test is used to compare the proportions of patients with pTRG3, the proportion of patients with TRG on MRI (mrTRG) (1–5) after 2 cycles/4 cycles of CAPOX, and the proportion of patients with pTRG (0–2). Survival of patients (OS, DFS) is compared using Kaplan–Meier analysis. Statistical significance is defined as a *p*-value less than 0.05. Especially, in the 4 cycles of the CAPOX group, patients who receive less than 3 cycles of chemotherapy due to adverse effects or drop-out will be analyzed as the 2 cycles of the CAPOX group; others will be analyzed in the 4 cycles of the CAPOX group analysis.

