### Patients and study design

This is a multicenter, prospective, non-inferior, randomized controlled study initiated by West China Hospital of Sichuan University and designed to be conducted in fourteen hospitals around China (Additional file 1).

Patients with low-risk and intermediate-risk stage II/III rectal cancer are designed to be included in the study. The flow diagram has been shown in Fig. 1. In brief, patients diagnosed with rectal cancer will be evaluated by enhanced abdominal CT, pelvic MRI, and transrectal ultrasonography (TRUS) and staged according to the European Society for Medical Oncology (ESMO) guidelines [19]. Eligible patients will be randomized to accept 2 or 4 cycles of pre-preoperative CAPOX. Re-evaluation will be performed after 2 cycles of CAPOX (2 and 4 cycles group) and 4 cycles of CAPOX (4 cycles group). MrTRG will be recorded and verified by pTRG after TME surgery. Detailed criteria for mrTRG and pTRG have been listed in Additional files 2 and 3, respectively.

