### Randomization and intervention

Each sub-center will be responsible for potential enrollment and consent-taking. Central randomization will be performed as soon as the enrollment is determined using the central automated randomization system offered by the O-trial online system (https://plus.o-trial.com/). Sub-center will upload the information of eligible patients on the O-trial system, which will sequentially number and randomize the uploaded patients into 2 or 4 cycles of CAPOX in a 1:1 ratio automatically. No stratification is included in the current study.

Patents in both groups will undergo TME surgery after 2 or 4 of CAPOX. Each cycle of CAPOX includes oxaliplatin 130 mg/m^2^, once daily on day 1, every 21 days and capecitabine 1000 mg/m^2^, twice daily on days 1 to 14, every 21 days. TME surgery was performed by experienced colorectal surgeons 2–3 weeks after the last cycle of preoperative CAPOX.

Postoperative adjuvant treatment will be performed according to the ESMO and Chinese guidelines for colorectal cancer [19, 20]. Based on the pathological stage, patients with a positive CRM or N2 stage would be recommended to undergo postoperative radiotherapy. Adjuvant chemotherapy was recommended for N + patients. The long-term survival of the patients will be followed up.

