### Data collection

Clinical, imaging, and follow-up data will be collected prospectively in the case report forms (Additional file 4) and reserved in the O-trial online database (https://plus.o-trial.com/), which is daily maintained by [name] and [name]. The O-trial online database is a secure, password-protected database and can be only accessible to authorized project staff.

Details of the evaluation items and time points have been shown in Table 2. During CAPOX, blood routine and biochemistry will be examined weekly to detect potential hematopoietic inhibition or liver or kidney function impairment. Tumor markers, at least including CEA and CA19-9, will be recorded every cycle. Imagological examination, including chest CT, abdominal enhanced CT, rectal MRI, and TRUS will be re-evaluated every 2 cycles.

**Table 2 Tab2:** Details of the evaluation items and time points

	Screening	After 2 cycles of CAPOX (4 cycles)	Preoperative evaluation	Intraoperative evaluation	Postoperative evaluation	Follow-up visit
Colonoscopy	×					
Chest CT	×	×	×			×
Abdominopelvic enhanced CT	×	×	×			×
Pelvic MRI	×	×	×			
TRUS	×	×	×			
Blood routine	×	×	×			×
Blood biochemical indicators	×	×	×			×
Tumor markers^a^	×	×	×			×
Intraoperative complications				×		
Blood loss				×		
Operation time				×		
Surgical approach				×		
Perioperative complications					×	
Patient recovery					×	
Hospitalization time					×	
pTRG					×	

*TRUS* Transrectal ultrasonography, *pTRG* Pathological tumor regression grade

^a^At least includes CEA and CA19-9

Surgical information including tumor location and involvement, intraoperative stages, lymph node metastasis, operation times, intraoperative time, and complications will be recorded in detail in the surgical records. Perioperative complications are stratified by the Clavien-Dindo system. Resected rectal specimens will be fixed on a foam plate and sent to pathologists to determine the circumferential resection margin (CRM) and pTRG).

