Follow-up is set throughout the whole trial (Additional file 5). In the preoperative CAPOX process, included patients will be asked to finish a series of questionnaires about quality of life (QOL) and tumor or NCT-related symptoms each cycle. Postoperative follow-up is set at 3 months after surgery, every 6 months in the first 5 years, and every year in subsequent years. QOL, blood tests, and CT imaging are also included in each follow-up. Adverse effects of postoperative adjuvant chemotherapy will also be recorded.

QOL is measured based on EORTC QLQ-C30 [21, 22], the EORTC QLQ-CR29 questionnaire [23], the International Prostatic Symptom Score (I-PSS) [24], and the sexual function evaluation questionnaire, which will be gathered by physician visits, mail, or WeChat and recorded in the online system for further analysis. Radiological examinations will be individually assessed by two radiologists blinded to the groups. Tumor imaging data, such as tumor long diameter, tumor volume, ADC value, and DWI value, will be collected and mrTRG will be determined accordingly. When a discrepancy arose, the imaging scans will be reviewed by two experienced radiologists in West China Hospital to reach a consensus. Based on MRI imaging, tumor response to NCT is classified into grades 1–5 (complete, good, moderate, slight and no response), and mrTRG4 and mrTRG5 represent a poor response to NCT. Criteria of the mrTRG have been listed in Additional file 2. Pathology examinations are performed by each sub-center and verified by the primary center to determine the pTRG (0–3). A pTRG3 represents poor tumor response to NCT. Specific standards of pTRG have been shown in Additional file 3.

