### Sample size calculation

According to phase II trial [16], the proportion of patients who had poor pathological remission (pTRG 3) after 4 cycles of CAPOX was 27.9%. The proportion of pTRG3 after 2 cycles of CAPOX is expected to increase by no more than 10%. The non-inferiority test is used with *α* = 0.05, (1-β) = 0.8, and the non-inferiority margin (hazard ratio) value δ is set as 0.05. Pearson chi-square test is used to calculate the sample size required for the experiment, and 249 samples are required for each group calculated by a normal approximation algorithm [25]. Ten percent of patients are estimated to withdraw from the group or lost to follow-up; 277 patients are needed in each group. The planned enrollment time is 2.5 years, and the total number of patients is about 554 cases. Meanwhile, it is assumed that the dropout rate of patients in the 4 cycles of the CAPOX group is about 6% due to intolerance of chemotherapy. Therefore, it is estimated that 294 patients would be included in the 2 cycles of the CAPOX group and 260 patients in the 4 cycles of the CAPOX group.

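### The primary pTRG3 comparison is an unadjusted two-by-two test that ignores baseline tumour features known before randomisation; a short covariate-adjusted risk difference would be a cheap, modest gain in precision

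*Protocol article*

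**What the plan says.** The Data-analysis section of the protocol article names the primary test: Fisher's "exact test or the chi-square test is used to compare the proportions of patients with pTRG3". It mentions no covariate, no centre term and no confidence interval for the difference.

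The Randomization and intervention section says the system will "randomize the uploaded patients into 2 or 4 cycles of CAPOX in a 1:1 ratio automatically" and adds "No stratification is included in the current study". The trial is "designed to be conducted in fourteen hospitals around China". On grading of the endpoint, the Data collection section says "Pathology examinations are performed by each sub-center and verified by the primary center".

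Location relative to the peritoneal reflection, T substage, N stage and EMVI all appear in the risk definition under Patients and study design and in inclusion criterion 2 of Table 1. They are therefore assessed at screening for every patient. Table 2 also places pelvic MRI, TRUS and tumour markers at screening.

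**The concern.** When baseline features predict a binary endpoint, a risk difference standardised from a model containing them targets the same quantity as the crude difference between randomised arms. In large samples its variance is no greater. Here those features are recorded anyway, and nothing in the allocation balances them. At stake is the width of the interval on which non-inferiority would be judged, in a trial whose sample size was set to give 80% power and no more.

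The form of the analysis matters too. The objective is non-inferiority, which needs an estimate with an interval to set against a margin. A standardised risk difference supplies that; a test of difference at p < 0.05 does not. An unadjusted risk difference with its interval would also supply it, so this benefit comes from using an interval and not from the adjustment.

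**Working it through.** **Inputs from the Sample size calculation section.** The article states that "the proportion of patients who had poor pathological remission (pTRG 3) after 4 cycles of CAPOX was 27.9" per cent. It gives an expected increase of no more than 10%, alpha 0.05 (sidedness not stated), power 0.8, 249 per group, and 277 per group after 10% dropout. It also states a margin of 0.05, labelled a hazard ratio.

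**1. Reproducing 249.** Take 27.9% in both arms, a 0.10 absolute margin and one-sided alpha 0.05:

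n = 2 × 0.279 × 0.721 × (1.645 + 0.842)² / 0.10² = 0.4023 × 6.183 / 0.01 = 248.7, so 249.

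249 / 0.9 = 276.7, so 277 per group and 554 in total. Both figures match. With the written 0.05 margin the same formula gives 995 per group. The 80% baseline below therefore assumes the 0.10 margin.

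**2. Unadjusted power at 249 per group.** SE = √(2 × 0.279 × 0.721 / 249) = 0.0402. Power = Φ(0.10 / 0.0402 − 1.645) = 0.800.

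**3. Power after adjustment.** If adjustment removes a share v of the variance, SE becomes 0.0402 × √(1 − v). The matching number of extra patients per group is 249 / (1 − v) − 249. The values of v are assumptions.

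| v | SE | Power, margin 0.10 | Equivalent extra patients per group |
|---|---|---|---|
| 0 | 0.0402 | 80.0% | 0 |
| 0.025 | 0.0397 | 80.9% | 6 |
| 0.05 | 0.0392 | 81.8% | 13 |
| 0.10 | 0.0381 | 83.6% | 28 |

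For orientation, take a normally distributed linear predictor on the logit scale and a 27.9% event rate. Baseline AUCs of 0.60, 0.65 and 0.70 then correspond to v of about 2.6%, 5.8% and 10.4%.

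**4. Finite-sample cost.** About 498 × 0.279 = 139 events are expected. Simulations with 498 patients, using assumed covariate effects, gave the following:

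- Four covariates, no centre terms: variance changes from about +1% (nothing prognostic) to −8%.
- With 13 fixed centre terms added: increases of about 3% to 4.5% when nothing is prognostic. In one such run, baseline AUCs of 0.59, 0.62, 0.66 and 0.70 gave changes of about +2%, +1%, −3% and −8%.
- With shrunken centre effects instead: about +1.4% when nothing is prognostic.

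In power terms, a 1% increase gives Φ(0.10 / (0.0402 × √1.01) − 1.645) = 79.7%. A 4.5% increase gives 78.5%.

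**5. The written margin.** With 0.05 in place of 0.10, power at 249 per group is Φ(0.05 / 0.0402 − 1.645) = 34.4%. It is 36.9% at v = 0.10 and 40.0% at v = 0.20.

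**The case against.** The strongest reply is that nothing here is wrong. Under unstratified 1:1 randomisation a two-sample comparison of proportions is valid, and it matches the Pearson chi-square basis of the sample size. Covariate choice is often left to an analysis plan, which is not shown. All of that stands, and it is why this is an improvement and not a correction. It does not dispose of the point, because the article names the primary test outright.

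The second reply is that the gain is speculative. The documents give no baseline AUC or R². Their only AUC, 0.862 in the Background, concerns morphological change after 2 cycles, which comes after randomisation and cannot serve as a baseline covariate. The Background also says there is no reliable preoperative way to assess response, and the narrow eligibility limits the spread of the covariates. This stands as well: the gain may be nil.

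Three stronger readings are tempting, and the documents support none of them.

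- **That lack of stratification biases the crude test.** Chance imbalance is already reflected in its standard error.
- **That adjustment can only help.** Equal or smaller variance is a large-sample result. At 498 patients a model with 13 fixed centre terms can lose precision.
- **That local grading obliges a centre term in the primary model.** The size of any between-centre variation is not given, and the primary center verifies the grades.

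**Conclusion.** The point holds as a modest, low-cost efficiency improvement. Under assumed variance reductions of 2.5% to 10%, power rises from 80% to about 81% to 84%. That rests on a 0.10 absolute margin, one-sided alpha 0.05, 27.9% in both arms and 249 evaluable patients per group. At one-sided 0.025 the corresponding figures are 70.1% unadjusted and 71.2% to 74.6% adjusted. If the four covariates are uninformative, the cost is about 1% in variance.

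The equivalence of the crude and standardised differences also assumes that arms are compared as randomised. The Data-analysis section instead moves 4-cycle patients who receive fewer than 3 cycles into the 2-cycle group. The sample size section expects 294 and 260 in place of 277 and 277, a shift of 17. Covariate adjustment does not repair that rule.

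A reader might also infer that adjustment would rescue the trial under the written 0.05 margin. It would not: power stays at or below 40% even at an assumed 20% variance reduction.

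**What to change.** In the Data-analysis section, replace the crude primary test with the following:

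- **Estimate.** The pTRG3 risk difference, 2 minus 4 cycles, with arms as randomised, standardised from a logistic model containing arm, location relative to the peritoneal reflection, cT substage, cN and EMVI. Fix the coding in advance: under the eligibility definition T3c and T4a occur only above the reflection, so location and substage overlap.
- **Decision rule.** Non-inferiority is concluded if the upper confidence limit lies below the margin. First reconcile the 0.05 and 10% figures, state the margin as an absolute risk difference, and set the confidence level to match a stated one-sided alpha.
- **Sensitivity analysis.** The unadjusted risk difference with its interval.
- **Centre.** No 13 fixed centre terms. Use a random centre effect, or keep centre for a sensitivity analysis.

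Randomisation need not change. The cost is one paragraph of analysis wording and a few lines of code, with no new data, patients or procedures. The covariate list must be fixed before pTRG results by arm are seen.

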## Methods/design

### Objective

The primary objective of this study is to prospectively evaluate that the pathological response rate after 2 cycles of CAPOX is not inferior to that of 4 cycles in patients with low-risk and intermediate-risk stage II/III rectal cancer, which may provide evidence for the feasibility of early identification of chemotherapy-insensitive population.

The secondary objectives are as follows: (1) to explore the difference in clinical remission rate between 2 and 4 cycles of CAPOX in patients with low-risk and intermediate-risk stage II/III rectal cancer; (2) to explore the effectiveness/ineffectiveness of NCT at early cycles (after 2 cycles of CAPOX) in predicting the long-term prognosis (3 years overall survival (OS)/disease-free survival (DFS)); (3) to confirm the perioperative safety of NCT alone; (4) to construct a model using 2-cycle imaging indicator to predict a 4-cycle pathological remission; and (5) to explore the feasibility of artificial intelligence (AI)-assisted imaging indicators to predict pTRG after NCT.

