### Endpoints

The primary endpoint is the proportion of patients with pTRG3, which is determined postoperatively by each sub-center and verified by the primary center.

The secondary endpoints include (1) the proportion of patients with TRG on MRI (mrTRG) (1–5) after 2 cycles/4 cycles of CAPOX; (2) the proportion of patients with pTRG (0–2); (3) survival prognosis of patients with different pTRG, containing disease-free survival (DFS), local recurrence rate (LR), distant recurrence rate (DR), and overall survival (OS); (4) 3-year DFS and OS of patients with different pTRG; (5) the predicted imaging indicators of pTRG; (6) the accuracy of pTRG judged by imaging; (7) the adverse effects of chemotherapy; (8) the incidence of perioperative complications; and (9) the QOL of patients during chemotherapy and after surgery.

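### The primary endpoint, pTRG3, is assigned a test of equality at p < 0.05, although the objective and the sample size are for non-inferiority

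*Protocol article*

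**What the plan says.** All places are in the protocol article.

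- **Objective.** The trial is to show that "the pathological response rate after 2 cycles of CAPOX is not inferior to that of 4 cycles".
- **Endpoints.** "The primary endpoint is the proportion of patients with pTRG3", a binary and unfavourable outcome.
- **Sample size calculation.** In the phase II trial the poor-response proportion was put at 27.9% with 4 cycles. For the shorter course the section adds: "The proportion of pTRG3 after 2 cycles of CAPOX is expected to increase by no more than 10" per cent. It also says that a non-inferiority test is used, with alpha 0.05, power 0.8 and a margin of 0.05 that it labels a hazard ratio. It does not say whether alpha is one-sided or two-sided. The result is 249 per group, raised to 277 per group (554 in total) for 10% loss, with projected group sizes of 294 and 260 after switching.
- **Data-analysis.** "the chi-square test is used to compare the proportions of patients with pTRG3", with Fisher's exact test as the alternative. The same sentence gives the same tests to two secondary endpoints (mrTRG grades, and pTRG 0–2). "Statistical significance is defined as a *p*-value less than 0.05". The section contains neither the margin nor a rule for concluding non-inferiority.

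**The concern.** A chi-square or Fisher test has equality of the two proportions as its null hypothesis. A non-inferiority trial must reject a different null: that 2 cycles is worse than 4 cycles by at least the margin. A p-value above 0.05 from the equality test only says that a difference was not detected. It does not say that a difference as large as the margin has been excluded.

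The sample size section and the analysis section therefore name different tests for the same endpoint. If the Data-analysis section is followed literally, the primary objective has no valid decision rule. At stake is the trial's main conclusion: whether the shorter course may be called not inferior.

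**Working it through.** **Inputs.** 4-cycle pTRG3 rate 27.9%, increase of 10 points, alpha 0.05, power 0.8, margin 0.05, 249 per group and 10% loss, all from Sample size calculation; p < 0.05 from Data-analysis. Assumptions: the 10% is read as absolute points, and the p < 0.05 threshold as two-sided.

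**1. Which test produced 249?** For non-inferiority with equal true rates,

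n = 2p(1 − p)(z_α + z_β)² / δ².

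- δ = 0.10, one-sided 0.05: 2 × 0.279 × 0.721 × (1.645 + 0.842)² / 0.01 = 0.4023 × 6.183 / 0.01 = 248.7, so **249**. Then 249 / 0.9 = 276.7, so 277, and 2 × 277 = 554. The plan's figures are reproduced.
- δ = 0.10, one-sided 0.025: 316 per arm.
- δ = 0.05, one-sided 0.05: 0.4023 × 6.183 / 0.0025, so 995 per arm.
- A difference test of 27.9% v 37.9%, without continuity correction: 272 per arm (one-sided) or 346 (two-sided).

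So the trial was sized as a one-sided 5% non-inferiority comparison with a 10-point margin.

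**2. The equality test when 2 cycles is truly 10 points worse (37.9% v 27.9%), 249 per arm.**

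- Pooled rate 0.329; null SE = √(2 × 0.329 × 0.671 / 249) = 0.0421; critical difference 1.96 × 0.0421 = 0.0825.
- True SE = √((0.379 × 0.621 + 0.279 × 0.721) / 249) = 0.0419.
- Power = Φ((0.10 − 0.0825) / 0.0419) = Φ(0.417) = 0.66, so the test is non-significant in about 34% of trials.

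Exact enumeration of the binomial outcomes gives the chance of a non-significant result:

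| Group sizes | Pearson | Fisher |
|---|---|---|
| 249 v 249 | 33.5% | 37.1% |
| 277 v 277 | 29.0% | 32.1% |
| 294 v 260 | 29.4% | 30.9% |

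**3. A non-inferiority test in the same situation.** Requiring the one-sided 95% upper limit of the risk difference to be below 0.10, at 249 per arm, passes this regimen in 4.9% of trials (2.5% with one-sided 0.025). With equal true rates its power is 80.2% (70.2% with one-sided 0.025).

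**4. Where the two rules part.** Take an observed 4-cycle rate of 27.9% and 249 per arm.

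- Non-inferiority at 10 points needs an observed excess below about 0.10 − 1.645 × 0.0409 = 0.033.
- The Pearson test stays non-significant up to an excess of about 1.96 × 0.0418 = 0.082.

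An observed excess between roughly 3.3 and 8.2 points is thus non-significant without showing non-inferiority.

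**The case against.** The strongest reply is that the article does name a non-inferiority test with a margin, under Sample size calculation, and that a condensed article may leave the confidence interval and its decision rule to the full protocol or the SAP. Both points have weight. The absence of a planned interval, taken alone, would not be a defect. But the Data-analysis section is not silent: it assigns a specific test to the primary endpoint, and that test answers a different question from the one the sample size assumes. A separate SAP could correct this, but the published text would still contradict itself.

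Three stronger readings are tempting and are not supported.

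- A reader might infer that the trial will call a non-significant result non-inferior. The article never says so. The 29% to 37% is the error rate under that reading, not a property of the plan as written.
- A reader might add that a regimen truly 5 points worse would be non-significant in 77% of trials at 249 per arm. With a 10-point margin, 5 points lies inside the tolerated loss, so that is not a rate of false non-inferiority.
- A reader might take "Pearson chi-square test is used to calculate the sample size required for the experiment" as proof that the trial was sized for a difference test. The 249 comes out exactly from a non-inferiority formula, so that sentence is not evidence for it.

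**Conclusion.** Wrong as written. The article sets a non-inferiority objective and sizes for it, then assigns the primary endpoint a test of equality that does not use the margin and cannot establish non-inferiority.

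The size is conditional. If non-significance were taken as non-inferiority, a regimen 10 points worse would pass about one time in three, against about one in twenty for the test the sample size implies. This rests on a true 4-cycle rate of 27.9%, a two-sided 0.05 threshold for the equality test, and a 10-point margin inferred from the 249. The article attaches the word margin to 0.05 instead, so the 5% comparator holds only if 10 points is confirmed. The mismatch of tests does not depend on which margin is chosen.

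**What to change.** 1. Settle the margin first. State one value on the risk-difference scale and remove the hazard-ratio label, which does not fit a binary endpoint. Ten points agrees with 249 per arm; 0.05 would need about 995.
2. State whether alpha is one-sided or two-sided. The 249 corresponds to one-sided 0.05, that is, the upper end of the two-sided 90% interval. One-sided 0.025 would need about 316 per arm.
3. Make the primary analysis the risk difference in pTRG3 (2-cycle minus 4-cycle) with an interval suited to proportions, for example Miettinen–Nurminen or Newcombe. Declare non-inferiority only if the upper limit is below the stated margin.
4. Keep the chi-square and Fisher tests of pTRG3 as descriptive only.

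The analysis change costs protocol and SAP wording and a few lines of code, with no new data. The interval may need software other than the packages named. The sample size is unaffected if 10 points and one-sided 0.05 are confirmed, and would have to be revisited otherwise. The Data-analysis rule that moves some 4-cycle patients into the 2-cycle group is a separate matter and is not resolved by this change.

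### Secondary endpoints: mrTRG 1–5 is ordered but gets a test that ignores order, and the plan does not say whether pTRG 0–2 is pooled; both are cheap to improve

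*Protocol article*

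**What the plan says.** All references are to the protocol article.

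- **Scales (Data collection).** On MRI, "tumor response to NCT is classified into grades 1–5 (complete, good, moderate, slight and no response"), with grades 4 and 5 counted as poor response. Pathological regression is graded 0 to 3, and grade 3 is the poor-response category.
- **Endpoints.** The primary endpoint is the proportion with pTRG3. The first secondary endpoint is mrTRG (1–5). The second is "the proportion of patients with pTRG (0–2"). The text does not say whether this is one pooled proportion or one proportion per grade.
- **Tests (Data-analysis).** Fisher's exact or the chi-square test is named for pTRG3, for "the proportion of patients with TRG on MRI (mrTRG) (1–5) after 2 cycles/4 cycles of CAPOX", and for pTRG (0–2). The Mann–Whitney test is named for continuous variables only. No trend, rank or ordinal-model analysis is given for either graded scale.
- **Imaging (Patients and study design).** Both arms are re-imaged after 2 cycles, and the 4-cycle arm again after 4.

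**The concern.** A chi-square test on a 2×5 table gives the same result however the five grades are arranged. It spreads its sensitivity over 4 degrees of freedom, although the likeliest effect of fewer cycles is a drift towards worse grades. For that kind of change a test that uses the order has more power.

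The pTRG (0–2) entry raises a different question. The scale has four grades and the primary endpoint is the fourth. If grades 0–2 are pooled, the second secondary endpoint repeats the primary with the sign reversed.

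These two endpoints are the main between-arm measures of depth of response. The trial argues that 2 cycles are not inferior to 4, so a non-significant result from a weak or redundant difference test could be taken as support for similarity.

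**Working it through.** **1. Sample size used.** The plan states "249 samples are required for each group calculated by a normal approximation algorithm", with "The non-inferiority test is used with *α* = 0.05, (1-β) = 0.8" and a 4-cycle pTRG3 rate of 27.9%. With equal true rates, an absolute margin of 0.10 and one-sided 0.05:

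n = (1.645 + 0.842)² × 2 × 0.279 × 0.721 / 0.10² = 6.183 × 0.4023 / 0.01 = 248.7, so 249.

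Then 249 / 0.9 = 276.7, so 277, and 2 × 277 = 554. The plan's figures are reproduced. (The printed margin of 0.05 would give 995 per arm; that is a separate matter.) This calculation covers the binary primary endpoint only. No power is stated for mrTRG or pTRG (0–2), so 249 per arm is borrowed below for illustration.

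**2. mrTRG: one case by hand.** The documents give no grade distribution and no effect size, so both are assumed. Take 10/25/35/20/10% in one arm and a common odds ratio of 1.5 towards worse grades. The cumulative odds 0.111, 0.538, 2.333 and 9 are divided by 1.5. The other arm then has 6.9/19.5/34.5/24.8/14.3%.

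- *Unordered chi-square, 4 df.* λ = 249 × Σ(p − q)²/(p + q) = 249 × 0.0253 = 6.3. The critical value is 9.49, and power is **49%**.
- *Rank test (Whitehead's approximation).* V = n₁n₂N / [3(N + 1)²] × (1 − Σp̄³) = 41.33 × (1 − 0.0666) = 38.6. Then ln(1.5) × √38.6 − 1.96 = 0.405 × 6.21 − 1.96 = 0.56, and power is **71%**.

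**3. mrTRG: range by simulation** (249 per arm, two-sided 0.05). Five assumed distributions were used: 10/25/35/20/10, 20 in each grade, 20/35/25/15/5, 5/20/40/25/10 and 20/30/30/15/5.

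| Common odds ratio | Unordered chi-square | Rank test |
|---|---|---|
| 1.3 | 21–22% | 36–38% |
| 1.5 | 48–51% | 70–73% |
| 1.8 | 83–86% | 95–96% |

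**4. Where the advantage reverses.** For an assumed change that is not in one direction (10/25/35/20/10 against 5/35/30/22/8), chi-square has 72% power and the rank test 7%.

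**5. pTRG (0–2), if pooled.** In every patient with a pTRG, the proportion in 0–2 is 1 minus the proportion in 3. Take 94/249 against 69/249 with pTRG3, close to 37.9% and 27.9%:

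χ² = 498 × (94 × 180 − 155 × 69)² / (249 × 249 × 163 × 335) = 5.70, p = 0.0170.

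Swapping the two columns leaves this unchanged. Fisher's p is 0.0218 both ways.

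**6. pTRG on its full scale.** The control arm is assumed at 21.3/25.4/25.4/27.9%. The first figure is the phase II pCR rate, the last the phase II pTRG3 rate, and the middle grades are split evenly by assumption.

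| Assumed change | pTRG3 alone (same as pooled 0–2) | Chi-square, 3 df | Rank test |
|---|---|---|---|
| Common odds ratio 1.58 (pTRG3 27.9% to 37.9%) | 67–68% | 65–66% | 80–82% |
| pTRG3 fixed; 10 points move from grade 0 to grade 2 | 5% | 84% | 50% |

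In the second row the pooled endpoint rejects at its error rate only. Either full-scale analysis can detect the change, and there the unordered one does better.

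**The case against.** **The chi-square test is not an error.** It keeps its type I error on ordered grades. The matching secondary objective is exploratory and worded as a rate, and the plan defines a poor-response cut (mrTRG 4–5) for which a chi-square test is natural. This stands: the mrTRG point is about efficiency, not validity.

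**The power gap rests on assumptions that favour the rank test.** This also stands. Proportional odds was assumed, the distributions are not from the documents, and steps 4 and 6 show the reverse for other patterns. A reader might infer that a rank test is always better; the figures do not support that.

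**A reader might infer that pTRG (0–2) certainly duplicates the primary endpoint.** The documents do not settle this. The Background's hope for grade 2 or better and the response-rate objective favour pooling. But mrTRG (1–5) has the same form and cannot be pooled, because its pooled proportion is always 100%. Read the same way, pTRG (0–2) means a proportion for each of grades 0, 1 and 2. With pTRG3 that covers the whole scale, and a move from 0–1 to 2 would show. What remains is an ambiguity to resolve.

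**Percentages will be reported anyway.** Data-analysis says categorical variables are shown as percentages, so a shift in mrTRG should be visible whatever the p-value. That softens the consequence, but it gives no ordered effect estimate with an interval.

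**Conclusion.** This is a low-cost improvement confined to two secondary endpoints.

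- **mrTRG 1–5:** the named test is valid but ignores the order. Under assumed one-directional shifts it gives up about 10 to 22 percentage points of power at 249 per arm, with about 48–51% against 70–73% at a common odds ratio of 1.5. There is no such loss, and possibly a gain, when the change is non-monotone or confined to a few grades.
- **pTRG (0–2):** the plan does not say whether it is pooled. If it is, it adds nothing to the primary endpoint. If it is per grade, it adds information, but the named test again ignores the order. An ordered analysis of the full 0–3 scale is sound under either reading.

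Nothing here touches the primary analysis, the stated power or the 249/277/554 figures.

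**What to change.** 1. **Data-analysis, mrTRG.** Compare mrTRG 1–5 between arms with a Wilcoxon rank-sum test, or with a proportional-odds model reporting the common odds ratio and its 95% confidence interval. State which MRI is used. After 2 cycles both arms have had the same planned treatment, so only the last preoperative MRI compares 2 with 4 cycles.
2. **Endpoints and Data-analysis, pTRG.** State whether pTRG (0–2) is pooled. If it is, replace it with the full ordered pTRG 0–3 distribution, analysed in the same way.
3. **Both scales.** Keep counts and percentages per grade, with the chi-square test as a supporting analysis, so that changes without a single direction are not lost.

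**Cost.** A few sentences. The plan already names the Mann–Whitney test, and neither data collection nor sample size changes. The downsides are lower power for non-ordered changes, the proportional-odds assumption if the model is used, and a minor amendment. If that amendment counts as substantive, the protocol requires ethics submission and a registry update.
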